# Non-inferiority of low-dose compared to standard high-dose calcium supplementation in pregnancy: study protocol for two randomized, parallel group, non-inferiority trials in India and Tanzania

**DOI:** 10.1186/s13063-021-05811-7

**Published:** 2021-11-24

**Keywords:** Calcium, Dietary supplements, Pregnancy, Pregnancy complications, Pre-eclampsia, Pregnancy-induced hypertension, Preterm birth, Non-inferiority trial

## Abstract

**Background:**

Hypertensive disorders of pregnancy are important causes of maternal morbidity and mortality, as well as preterm birth, the leading cause of death for children under 5 years globally. The World Health Organization currently recommends that pregnant women receive high-dose calcium supplementation (1500–2000 mg elemental calcium) for prevention of preeclampsia in populations with low dietary calcium intake. Trials of low-dose calcium supplementation (< 1000 mg elemental calcium/day) during pregnancy have also shown similar reductions in the risk of preeclampsia; however, no trials to date have directly compared low-dose to the standard high-dose calcium supplementation. Our objective is to assess the non-inferiority of low-dose as compared to standard high-dose calcium supplementation in pregnancy.

**Methods/design:**

We will conduct two independent trials in Bangalore, India (*n* = 11,000 pregnancies), and Dar es Salaam, Tanzania (*n* = 11,000 pregnancies). The trial designs are individually randomized, parallel group, quadruple-blind, non-inferiority trials of low-dose calcium supplementation (500 mg elemental calcium/day) as compared to standard high-dose calcium supplementation (1500 mg elemental calcium/day) among nulliparous pregnant women. Pregnant women will be enrolled in the trial before 20 weeks of gestation and will receive the randomized calcium regimen from randomization until the time of delivery. The co-primary outcomes are (i) preeclampsia and (ii) preterm birth; we will test non-inferiority of the primary outcomes for low-dose as compared to the standard high-dose supplementation regimen in each trial. The trials’ secondary outcomes include gestational hypertension, severe features of preeclampsia, pregnancy-related death, third trimester severe anemia, fetal death, stillbirth, low birthweight, small-for-gestational age birth, and infant death.

**Discussion:**

The trials will provide causal evidence on the non-inferiority of low-dose as compared to the standard high-dose supplementation in India and Tanzania. A single tablet, low-dose calcium supplementation regimen may improve individual-level adherence, reduce programmatic costs, and ultimately expand implementation of routine calcium supplementation in pregnancy in populations with low dietary calcium intake.

**Trial registration:**

ClinicalTrials.gov identifier: NCT03350516; registered on 22 November 2018. Clinical Trials Registry—India identifier: CTRI/2018/02/012119; registered on 23 February 2018.

Tanzania Medicines and Medical Devices Authority Trials Registry identifier: TFDA0018/CTR/0010/5; registered on 20 December 2018.

**Supplementary Information:**

The online version contains supplementary material available at 10.1186/s13063-021-05811-7.

## Background

Hypertensive disorders of pregnancy (HDP), including chronic hypertension, gestational hypertension, preeclampsia, eclampsia, and preeclampsia superimposed on chronic hypertension are among the leading causes of maternal and perinatal morbidity and mortality [1–3]. It is estimated that approximately 15% global maternal deaths (~ 30,000 deaths per year) are attributed to hypertensive disorders of pregnancy and that 2–8% of all pregnancies are complicated by preeclampsia with variation by country and context [3–5]. Further, HDP are well-established risk factors for preterm birth which is now the leading cause of death for children under 5 years globally [6–8]. Therefore, addressing the large burden of hypertensive disorders of pregnancy will be essential to reach global maternal and child health goals.

Calcium supplementation in pregnancy has been established as an intervention to reduce the incidence of preeclampsia and preterm birth in populations with low dietary calcium intake [9, 10]. The most recent Cochrane Review meta-analyzed 13 randomized controlled trials of high-dose prenatal calcium supplementation (≥ 1000 mg elemental calcium/day) that included over 15,000 pregnancies and determined that calcium supplementation approximately halved the risk of preeclampsia as compared to placebo (relative risk (RR): 0.45, 95% confidence interval (CI) 0.31 to 0.65) and that the beneficial effects appeared to be larger in populations with low calcium diets [9]. High-dose calcium supplementation also reduced the risk of the composite outcome of maternal death or severe morbidity (RR 0.80, 95% CI 0.66 to 0.98) and reduced the risk of preterm birth (RR 0.76, 95% CI 0.60 to 0.97) [9].

The World Health Organization (WHO) currently recommends that pregnant women receive daily high-dose calcium supplementation (1500–2000 mg oral elemental calcium) for prevention of preeclampsia in populations with low dietary calcium intake [10]. The WHO suggested dosing scheme for calcium supplementation recommends dividing the total dose into three doses that are preferably taken at mealtimes. Further, WHO notes that due to potential negative interactions between iron-containing supplements and calcium supplements, that these two mineral supplements preferably be taken several hours apart [10]. Despite proven efficacy and the WHO recommendation, calcium supplementation in pregnancy is not currently implemented in many low and middle-income countries (LMIC). Two important barriers to implementation of calcium supplementation in pregnancy are the complexity of the dosing scheme and the cost (estimated to be $11.50 per pregnancy for a 6-month supply) of high-dose calcium supplementation regimens [10–13].

The most recent Cochrane review also identified twelve randomized trials of low-dose calcium supplementation (< 1000 mg elemental calcium/day) that included a total of ~ 2300 pregnant women [9]. Low-dose calcium supplementation (with most trials using 500 mg/day) significantly reduced the risk of preeclampsia as compared to placebo (RR 0.38, 95% CI 0.28 to 0.52), and the magnitude of the effect was similar to the effect of high-dose calcium supplementation as compared to placebo [9]. There was no statistically significant effect of low-dose calcium supplementation on preterm birth (RR 0.83, 95% CI 0.34–2.03); however, statistical power was limited, and the wide confidence intervals are consistent with a similar effect as the high-dose calcium supplementation compared to placebo. As a result, it is possible that low-dose and high-dose calcium supplementation may have similar beneficial effects on preeclampsia, preterm birth, and other maternal and child health outcomes. If a once daily low-dose calcium supplementation regimen in pregnancy can provide non-inferior benefits on preeclampsia and preterm birth compared to the recommended high-dose calcium supplementation with a three-dose daily scheme, it may help overcome adherence concerns and barriers for programs to implement routine calcium supplementation in pregnancy.

Our objective is to generate causal evidence for decision-making on the non-inferiority of low-dose as compared to the standard high-dose calcium supplementation for pregnant women in populations with low dietary calcium intake. We will conduct two individually randomized, parallel group, non-inferiority trials of low-dose 500 mg calcium supplementation as compared to standard high-dose 1500 mg calcium supplementation among nulliparous pregnant women in Bangalore, India and Dar es Salaam, Tanzania. The co-primary outcomes are preeclampsia and preterm birth. We will conduct two independent trials in Tanzania and India due to potential differences in dietary calcium intake, the risk and etiology of preeclampsia and preterm birth, and other factors that vary by setting that may result in differences in the non-inferiority of low-dose calcium supplementation. Further, vitamin D is recommended to be provided in combination with calcium supplements in pregnancy in India but not Tanzania. It is also important to provide comparable evidence in the context of South Asia and sub-Saharan Africa to better inform global decision-making on low-dose versus high-dose calcium supplementation during pregnancy.

## Methods

### Study design

We will conduct two independent trials in India and Tanzania. Each will be an individually randomized, parallel group, non-inferiority trial of low-dose 500 mg calcium supplementation versus standard high-dose 1500 mg calcium supplementation for nulliparous pregnant women. The eligibility criteria, intervention, follow-up methods, and outcome definitions have been unified between the two trials; however, each trial will be conducted, analyzed, and reported separately. The first participant was enrolled in the India trial on November 30, 2018, and follow-up data collection is planned to continue through August 2022. The first participant was enrolled in the Tanzania trial on March 22, 2019, and follow-up data collection is planned to continue through November 2022. This trial protocol was written following the Standard Protocol Items: Recommendations for Interventional trials (SPIRIT) checklist (see Additional file 1).

### Study settings

The trial in India (clinicaltrials.gov identifier: NCT03350516; Clinical Trials Registry—India identifier: CTRI/2018/02/012119) will be conducted in urban Bengaluru at 11 health facilities that provide antenatal care within the Greater Bengaluru Metropolitan Corporation system (locally referred to as the Bruhat Bengaluru Mahanagar Palike (BBMP)) (clinicaltrials.gov identifier: NCT03350516 and Clinical trials registry—India identifier: CTRI/2018/02/012119). The trial in Tanzania will be conducted in urban Dar es Salaam at 6 health facilities that provide antenatal care (clinicaltrials.gov identifier: NCT03350516 and Tanzania Medicines and Medical Devices Authority Trials Registry identifier: TFDA0018/CTR/0010/5).

### Eligibility criteria and recruitment

The trial flow diagram is presented in Fig. 1. The India and Tanzania trials have the same eligibility criteria for participant enrollment. The inclusion criteria are (a) nulliparous pregnancy, (b) attend first antenatal care visit at the study clinic, (c) less than 20 weeks gestation based on last menstrual period at the time of randomization, (d) ≥ 18 years old, (e) intend to stay in study area until 6 weeks postpartum, and (f) provide written informed consent. Pregnant women will be excluded if they have a (a) history, signs, or symptoms of nephrolithiasis, (b) prior diagnosis of parathyroid disorder or thyroidectomy, or (c) disease that requires digoxin, phenytoin, or tetracycline therapy. Trained research staff will assess eligibility criteria for all participants presenting to the antenatal care clinic and ask potential participants for written informed consent for trial enrollment. Participants will also be asked for their written consent for use of their data and biological specimens (if applicable) in ancillary studies. During the conduct of the trial, the investigators will monitor monthly enrollment targets for the trials and may consider including additional study clinics to increase enrollment if recruitment is slower than expected.

**Fig. 1 Fig1:**
[figure not shown]
Trial flow diagram for the India and Tanzania trials

### Interventions

The India and Tanzania trials will assess the non-inferiority of a low-dose calcium supplementation regimen (500 mg elemental calcium/day) as compared to the standard high-dose calcium supplementation regimen (1500 mg elemental calcium/day). The trial regimens will be taken by pregnant women from randomization to the time of delivery (no postnatal supplementation). The standard high-dose 1500 mg calcium supplementation regimen was selected to align with WHO recommendations [10]. The low-dose calcium supplementation regimen was selected to align with low-dose calcium supplementation regimens used in prior low-dose calcium trials [9]. Both randomized groups will take three regimen tablets per day to have identical pill burden in both randomized groups. The trial regimen is manufactured by Influx Healthcare (Maharashtra, India).

Women in both randomized groups will receive a regimen box containing a 35-day supply of trial regimen in blister packs. Each blister pack will contain a 7-day supply of trial regimen (7 × 3 tablets per blister pack) with columns indicating morning, midday, and evening tablets. A diagram of the regimen blister pack for each trial is presented in Additional file 2. Participants in both groups will be counseled to take one trial regimen tablet in the morning, one in the midday, and one in the evening with meals and to take iron-containing prenatal supplements provided as standard of care several hours apart from the calcium trial regimen.

Standard high-dose calcium group (1500 mg elemental calcium/day): Pregnant women will be provided and counseled to take three regimen tablets daily with each containing 500 mg elemental calcium as calcium carbonate supplements daily (total of 1500 mg elemental calcium). In India, daily vitamin D_3_ supplementation (250 IU) is recommended to be taken with calcium supplements and therefore each tablet in the standard high-dose calcium group will also contain 83.3 IU of vitamin D_3_ for a total of 250 IU vitamin D_3_ daily [14]. In Tanzania, the supplements in the standard high-dose calcium group will not contain vitamin D_3_.

Low-dose calcium group (500 mg elemental calcium/day): pregnant women will be provided and counseled to take three regimen tablets each day with the first morning pill containing 500 mg elemental calcium as calcium carbonate, while the second (midday) and third (evening) tablets will be placebo supplements (total of 500 mg elemental calcium per day). The placebo tablets will be identical in all ways as compared to the calcium supplements (appearance, color, shape, size, weight, taste). In India, each of the three daily regimen tablets in the low-dose calcium group will also contain 83.3 IU of vitamin D_3_ for a total of 250 IU vitamin D_3_/day. Therefore, the daily vitamin D_3_ dose will be identical between standard high-dose and low-dose calcium groups in India. In Tanzania, the supplements in the low-dose calcium group will also not contain vitamin D_3_.

Multiple strategies will be used to improve adherence to interventions in India and Tanzania. At both sites, research staff will take a pill count at each study visit by counting the number of unconsumed tablets returned in the regimen blister packs. Study staff will counsel participants on taking the trial regimen and provide advice on overcoming barriers. At the India site, community health workers (accredited social health activists (ASHAs)) will also be engaged to promote regimen adherence during their routine home visits. At the Tanzania site, biweekly text message reminders for adherence and upcoming study visits will be sent. At both the India and Tanzania trial sites, reminder telephone calls will also be made prior participants’ scheduled visits by the research team and if the subject anticipates that she will not be able to attend the clinic visit or does not attend the clinic visit as planned, a home visit will be made by research staff. The research staff will provide the regimen, take pill counts, and conduct clinical assessments (including blood pressure and proteinuria) at home visits.

Participants may withdraw from the study at any time. In addition, study investigators or study physicians can decide that a participant should not continue to take the trial regimen or participate in the study if there are safety concerns or if continued participation does not appear in the best interest of the participant.

### Concomitant care provided during the trial

At each trial site, all participants will be provided with standard of care throughout follow-up according to the national guidelines for antenatal care for India and Tanzania. Standard of care provided by clinic staff in Tanzania includes provision of daily iron-folic acid (IFA) supplements containing 60 mg iron and 0.4 mg folic acid. In India, pregnant women receive daily supplements containing 60 mg of iron throughout pregnancy and pregnant women less than 14 weeks of gestation are initially given daily 5 mg of folic acid until the end of the first trimester followed by daily 0.4 mg folic acid until delivery. Participants will have access to study clinics for post-trial care through the routine health system.

### Assignment of interventions: allocation and blinding

In both trials, pregnant women who consent for enrollment will be individually randomized in a 1:1 ratio to either the (i) low-dose 500 mg calcium supplementation group or (ii) the standard high-dose 1500 mg calcium supplementation. The allocation sequence was generated by a statistician in Boston for each trial separately (India and Tanzania) using a computer-generated randomization list of 11,000 individuals with block randomization, stratified by study clinic. Two non-study staff hold the randomization list codes until completion of primary analyses or until requested by the Data and Safety Monitoring Board (DSMB). An independent study pharmacist in each country will privately prepare the 500 mg and 1500 mg regimen boxes with participant IDs based on the randomization list. At the randomization visit, research staff will assign pregnant women who are eligible and consent for trial randomization to the next available participant ID which corresponds to a set of pre-labeled regimen boxes. The trial statistician and data analysts will also be blinded to treatment allocation for the primary statistical analysis. As a result, the trial is quadruple blind with all trial participants, research staff, and care providers, Investigators, outcome assessors, and trials statistician and data analysts being unable to determine the allocated trial arm for any trial participant or identify trial participants who are on the same trial regimen. Further, the randomization procedures ensure complete allocation concealment. The DSMB, Institutional Review Boards (IRBs), attending physicians, and Principal Investigators may request to unblind a participant(s) allocated trial group during the trial for safety reasons.

### Sample size

The sample size for each trial will be 11,000 participants. Statistical power for the primary outcomes of preeclampsia and preterm birth was calculated using formulas for binomial outcomes in non-inferiority trials [15]. Power calculations assumed 1:1 randomization, a one-sided test with a type I error rate (α) of 0.05, and a 10% loss-to-follow-up rate (including pregnancy loss for preterm outcome). The non-inferiority margin for each primary outcome was selected by the trials’ Technical Advisory Group. The non-inferiority margin for preeclampsia was set at a relative risk of 1.54 for low-dose calcium as compared to the standard high-dose calcium based on the lower bound of the 90% confidence interval for the effect of standard high-dose calcium versus placebo on preeclampsia [9, 16]. The non-inferiority margin for preterm birth was set at a relative risk of 1.16 for low-dose calcium as compared to the standard high-dose calcium regimen to maintain 50% of the effect based on the point estimate of the relative risk for the effect of standard high-dose calcium versus placebo on preterm birth (relative risk = 1.32) [9, 16]. The exact cumulative incidence of preeclampsia and proportion of preterm birth in the standard high-dose calcium arm was not known for the India and Tanzania sites, and therefore, power calculations were presented for a plausible range of cumulative incidence of preeclampsia of 1.5 to 5% and a proportion of preterm birth of 10.0 to 13.5%. Table 1 presents statistical power in each trial for the plausible range of preeclampsia and preterm birth in the standard high-dose calcium group. For preeclampsia, each trial will have ~ 95% power if the cumulative incidence of preeclampsia is as low as 1.5% in the standard high-dose group and > 99.9% if the incidence is high at 5%. For preterm birth, each trial will have 84.3% power if the cumulative incidence is as low as 10% in the standard high-dose group and > 99.9% if the incidence is as high as 13.5%.

**Table 1 Tab1:** Statistical power for primary outcomes of preeclampsia and preterm birth for each trial site based on a one-sided test with a type I error rate of 0.05 (India = 11,000 participants; Tanzania 11,000 participants)

		Cumulative incidence of preeclampsia in standard high-dose calcium group (1500 mg/day)		
		1.5%	3%	5%
**Statistical power for preeclampsia**	Noninferiority margin—relative risk of 1.54	**95.3%**	**99.9%**	**> 99.9%**
		Proportion of preterm (< 37 weeks) in standard high-dose calcium group (1500 mg/day)		
		10.0%	12.5%	13.5%
**Statistical power for preterm birth**	Noninferiority margin—relative risk of 1.16	**84.3%**	**91.4%**	**93.3%**

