## Statistical methods

The India and Tanzania trials will be analyzed independently; however, the outcome definitions and statistical methods will be the same for both trials. An intent-to-treat (ITT) analysis will be the primary approach for all analyses and one-sided tests for non-inferiority with a type I error rate of 0.05 will be used. The ITT analysis for preeclampsia will include all randomized women and the preterm birth ITT analysis will include all livebirths. A complete case analysis will be used in the primary analyses.

For preeclampsia, we will use a log-binomial model with a fixed effect for study clinic to account for the stratified randomization scheme to produce relative risk estimates for the preeclampsia outcome for the low-dose as compared to the standard high-dose calcium supplementation group. The upper bound of the 90% confidence interval of the relative risk for preeclampsia will be compared with the prespecified noninferiority margin to assess non-inferiority. The primary analysis for preeclampsia will be among all randomized participants. We will conduct a sensitivity analysis for preeclampsia excluding pregnancy losses and participants who withdraw before 20 weeks gestation. In addition, we will also construct Kaplan–Meier curves with gestational age as the time metric to visualize the incidence of preeclampsia between randomized groups. We will present relative risks and 90% confidence intervals but will not formally test non-inferiority for any preeclampsia sensitivity analyses.

For preterm birth, a generalized estimating equation (GEE) analysis with the log link, a fixed effect for study clinic and a compound symmetry working correlation matrix to account for correlations due to multiple gestation will be used to construct relative risks for preterm birth among live births between randomized groups. The 90% confidence intervals of the relative risk will be compared with the prespecified non-inferiority margin to assess non-inferiority. We will conduct a sensitivity analysis for preterm birth among singleton pregnancies and will present relative risks and 90% confidence intervals but will not formally test non-inferiority.

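### Table 1's power values match a fixed risk-difference test, not the planned relative-risk test, whose power is lower: about 84% rather than 95.3% (preeclampsia, 1.5%) and 79% rather than 84.3% (preterm birth, 10%)

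*Protocol article*

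**What the plan says.** All references are to the protocol article.

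- **Size and error rate (Sample size).** "The sample size for each trial will be 11,000 participants". "Power calculations assumed 1:1 randomization, a one-sided test with a type I error rate (α) of 0.05", with "a 10% loss-to-follow-up rate (including pregnancy loss for preterm outcome").
- **Margins (Sample size, Table 1).** Both are ratios. "The non-inferiority margin for preeclampsia was set at a relative risk of 1.54 for low-dose calcium" against high-dose calcium, and the preterm row is headed "Noninferiority margin—relative risk of 1.16".
- **Stated power (Sample size, Table 1).** The text says that "each trial will have ~ 95% power if the cumulative incidence of preeclampsia is as low as 1.5"%. Table 1 gives 95.3%, 99.9% and >99.9% for preeclampsia at 1.5%, 3% and 5%, and 84.3%, 91.4% and 93.3% for preterm birth at 10.0%, 12.5% and 13.5%. The method is described only as formulas for binomial non-inferiority outcomes, by citation. No scale is named and no assumed true effect is given.
- **Planned test (Statistical methods).** For preeclampsia, a log-binomial model: "The upper bound of the 90% confidence interval of the relative risk for preeclampsia will be compared with the prespecified noninferiority margin". For preterm birth, a GEE with a log link: "The 90% confidence intervals of the relative risk will be compared with the prespecified non-inferiority margin to assess non-inferiority".

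No risk-difference margin appears anywhere in the article.

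**The concern.** A margin set as a relative risk and tested through a relative-risk confidence interval needs power computed for that test. If a ratio margin is first turned into an absolute difference at an assumed control risk, and that difference is then treated as fixed, the calculation answers a different question. In the planned test the difference that can be tolerated moves with the high-dose risk actually observed, and power is lower for it.

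The low-incidence cells matter most. The article says that the high-dose risks at the two sites were not known, and its text leads with power at the lowest plausible incidence, so those cells are its worst-case assurance. They are also the most overstated. In a non-inferiority trial an inconclusive result is read against the power to succeed: a failed margin looks like stronger evidence against the low dose at 95% power than at 84%.

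**Working it through.** **Inputs**

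- 11,000 per trial, 1:1, 10% loss (Sample size): 11,000 × 0.9 / 2 = 4,950 per arm.
- One-sided alpha 0.05 (Sample size): z = 1.645.
- Margins R = 1.54 and 1.16; high-dose risks p as in Table 1.
- True relative risk 1. This is an assumption: the article does not state it, but Table 1 is reproduced under it.
- Clinic effects and the correlation within multiple gestations are ignored.

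**Step 1. Reproduce Table 1.** Use a risk difference with fixed absolute margin (R − 1)p:

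Power = Φ[ (R − 1)p / √(2p(1 − p)/4950) − 1.645 ]

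- Preeclampsia, 1.5%: margin 0.54 × 0.015 = 0.0081; standard error 0.002443; ratio 3.315; Φ(1.670) = 95.3%.
- Preterm birth, 10%: margin 0.16 × 0.10 = 0.0160; standard error 0.006030; ratio 2.653; Φ(1.008) = 84.3%.

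The other four cells also match (table below).

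**Step 2. Power of the planned test.** On the log relative-risk scale:

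Power = Φ[ ln R / √(2(1 − p)/(4950p)) − 1.645 ]

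- Preeclampsia, 1.5%: ln 1.54 = 0.4318; standard error 0.1629; ratio 2.651; Φ(1.006) = 84.3%.
- Preterm birth, 10%: ln 1.16 = 0.1484; standard error 0.0603; ratio 2.461; Φ(0.816) = 79.3%.

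| Outcome, high-dose risk | Table 1 | Fixed risk difference | Log relative risk | Exact enumeration of the 90% RR upper limit |
|---|---|---|---|---|
| Preeclampsia 1.5% | 95.3% | 95.26% | 84.3% | 83.8% |
| Preeclampsia 3% | 99.9% | 99.90% | 98.4% | 98.2% |
| Preeclampsia 5% | >99.9% | >99.99% | 99.95% | 99.9% |
| Preterm 10% | 84.3% | 84.34% | 79.3% | 79.2% |
| Preterm 12.5% | 91.4% | 91.37% | 87.4% | 87.4% |
| Preterm 13.5% | 93.3% | 93.32% | 89.8% | 89.8% |

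The exact column sums binomial probabilities over both arms for the Wald interval.

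**Step 3. Where the gap comes from.** With equal risks, dividing the numerator and denominator in Step 1 by p gives the same standard error as in Step 2. The formulas then differ only in the numerator: R − 1 against ln R, that is 0.54 against 0.432 and 0.16 against 0.148. The gap is therefore larger for the wider margin.

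**Step 4. Alternatives.** At 4,950 per arm the Farrington–Manning ratio test gives 83.7% (preeclampsia, 1.5%) and 79.2% (preterm, 10%). A Blackwelder-type ratio contrast gives 81.8% and 79.0%. A log odds ratio gives 83.3% and 71.6%. A risk difference with the variance at p and Rp gives 90.4% and 82.1%. None reproduces the printed 95.3% and 84.3%.

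**Step 5. Text against table.** The Sample size text puts preterm power at 13.5% above 99.9%; Table 1 prints 93.3%. This contradiction needs no inference about the formula.

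**The case against.** **The basis of Table 1 is inferred.** This stands. The article names no scale, cites a source for the formula and does not state a true relative risk. The evidence is agreement in all six cells and the failure of every ratio-scale formula tried. That is strong, but it is not a statement by the authors.

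**The 10% loss may be pessimistic.** With no loss (5,500 per arm) the log relative-risk formula gives 87.5% for preeclampsia at 1.5% and 82.9% for preterm birth at 10%. Both remain below the stated values, although the preterm gap is then under 2 points.

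**Most of the shortfall is in one cell.** Largely true. Preeclampsia at 3% and 5% stays above 98%, and preterm birth loses about 3.5 to 5 points. The article sets no power target, so 79% breaches no stated threshold.

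**Nothing in the analysis is wrong.** Also true. Comparing a relative-risk limit with a relative-risk margin is coherent, and the type I error is unaffected.

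Three stronger readings are tempting, and the article supports none of them:

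- *The chance of overall success is only 67% at the low end* (0.843 × 0.793, against 0.953 × 0.843 = 80% from Table 1). This requires a rule that both margins be met, and independence of the two outcomes. The article plans a test of each co-primary outcome and states no combined rule. It also calls hypertensive disorders risk factors for preterm birth, so independence is doubtful.
- *The calculation takes the high-dose incidence as known without error.* It does not: the variance 2p(1 − p)/n carries sampling error from both arms. Only the absolute margin is held fixed.
- *The trials are too small.* Power for each outcome is still about 79% or more throughout the planning range.

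**Conclusion.** The point holds as an error in the stated power. Table 1 presents, under relative-risk margins, figures that the planned relative-risk test does not have. At the low end of the planning range the overstatement is 11 points for preeclampsia (95.3% against about 84%) and 5 points for preterm birth (84.3% against about 79%). The risk of missing true non-inferiority for preeclampsia at 1.5% is about 16% rather than 5%. For preterm birth at 12.5% and 13.5% the overstatement is about 4 points; for preeclampsia at 3% and 5% it is under 2 points.

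The corrected figures rest on a true relative risk of 1, 10% loss and one-sided alpha 0.05. The explanation of how Table 1 arose is an inference. The power of the planned test follows from the inputs whichever formula was used.

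**What to change.** In the Sample size section:

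1. Replace the Table 1 values with power for the planned relative-risk test: preeclampsia about 84 / 98 / 99.9% at 1.5 / 3 / 5%, and preterm birth about 79 / 87 / 90% at 10 / 12.5 / 13.5%.
2. Change the matching sentences. The preterm figure at 13.5% should become about 90%, in place of a value above 99.9% that contradicts even the present table.
3. State the scale of the calculation, the assumed true relative risk of 1, and that 10% loss leaves 4,950 per arm.
4. If joint power for the two outcomes is reported at all, give it only as conditional on a stated both-margins rule and on independence. Whether to adopt such a rule is a separate decision for the sponsor.

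The cost is one table and one paragraph. Sample size, margins and analysis stay as they are; the only drawback is that the stated figures become less favourable.

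### The sample size text gives power above 99.9% for preterm birth at 13.5% incidence; Table 1 gives 93.3% for the same case, and the stated design supports the table

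*Protocol article*

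**What the plan says.** The Sample size section fixes the inputs: "The sample size for each trial will be 11,000 participants". "Power calculations assumed 1:1 randomization, a one-sided test with a type I error rate (α) of 0.05", together with "a 10% loss-to-follow-up rate (including pregnancy loss for preterm outcome". For preterm birth, "The non-inferiority margin for preterm birth was set at a relative risk of 1.16", and the range considered for the high-dose arm is "a proportion of preterm birth of 10.0 to 13.5"%.

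The text then summarises the result at both ends of that range. At the low end, "each trial will have 84.3% power if the cumulative incidence is as low as 10"%. At the high end, power is "> 99.9% if the incidence is as high as 13.5"%.

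Table 1, to which the same paragraph refers the reader, has a preterm birth row labelled "Noninferiority margin—relative risk of 1.16". Its entries are 84.3%, 91.4% and 93.3% at 10.0%, 12.5% and 13.5%.

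**The concern.** Text and table agree at 10% and contradict each other at 13.5%, although margin, alpha and sample size are identical. One of the two figures must be wrong.

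Preterm birth is the more demanding of the two co-primary outcomes. Its margin is 1.16 against 1.54 for preeclampsia, and its power in Table 1 is lower throughout. A reader who takes the text at face value would conclude that, at an incidence near 13.5%, failure to show non-inferiority could hardly be chance if the two regimens are equivalent. That would distort the reading of an inconclusive preterm birth result in either trial.

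**Working it through.** **Inputs (Sample size section).** 11,000 per trial at 1:1 is 5,500 per arm. Less 10%, 5,500 × 0.9 = 4,950 evaluable per arm. One-sided alpha is 0.05, so z = 1.645. The margins are relative risks of 1.16 (preterm birth) and 1.54 (preeclampsia). The true relative risk is not stated; I take it as 1, the usual assumption in a non-inferiority calculation.

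**Step 1: reproduce Table 1.** On the risk-difference scale, with p the high-dose incidence and M the margin:

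power = Φ( (M − 1)p / √(2p(1 − p)/n) − 1.645 ), with n = 4,950.

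| Outcome | p | (M − 1)p | SE | z | Power | Table 1 |
|---|---|---|---|---|---|---|
| Preterm birth | 10.0% | 0.0160 | 0.00603 | 1.01 | 84.3% | 84.3% |
| Preterm birth | 12.5% | 0.0200 | 0.00665 | 1.36 | 91.4% | 91.4% |
| Preterm birth | 13.5% | 0.0216 | 0.00687 | 1.50 | 93.3% | 93.3% |
| Preeclampsia | 1.5% | 0.0081 | 0.00244 | 1.67 | 95.3% | 95.3% |
| Preeclampsia | 3% | 0.0162 | 0.00343 | 3.08 | 99.9% | 99.9% |
| Preeclampsia | 5% | 0.0270 | 0.00438 | 4.52 | above 99.9% | above 99.9% |

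All six entries reproduce. This identifies the formula and supports the assumed true relative risk of 1. The text figure at 13.5% is the outlier.

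**Step 2: power on the scale of the planned analysis.** Statistical methods compares the 90% confidence interval of a relative risk with the margin. On the log scale at p = 0.135:

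ln(1.16) / √(2 × 0.865/(4,950 × 0.135)) − 1.645 = 0.1484/0.0509 − 1.645 = 1.27, so power is 89.8%.

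**Step 3: look for a reading that gives 99.9% at 13.5%.**

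- *Other test forms, 4,950 per arm:* Wald test on the ratio contrast 89.6%, Farrington–Manning 89.8%, pooled two-proportion 91.9%.
- *One-sided alpha of 0.025:* 83.1% (log relative risk) to 88.2% (risk difference).
- *No loss to follow-up, 5,500 per arm:* 92.2% to 95.3% across the methods.
- *Both trials pooled, 9,900 per arm:* 99.3% (log relative risk) or 99.7% (risk difference). The trials are in any case to be analysed separately.

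**Step 4: what 99.9% would need.** By Table 1's method, n = (1.645 + 3.090)² × 2 × 0.135 × 0.865 / 0.0216², about 11,220 evaluable per arm, or about 24,900 enrolled per trial after allowing for 10% loss. On the log relative-risk scale it is about 13,040 per arm, or about 29,000 enrolled. With 4,950 per arm, the high-dose incidence would have to be about 26% (risk difference) to 29% (log relative risk), roughly twice the top of the stated range.

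**The case against.** The best case on the other side is that this is a slip in one clause with little resting on it. The supported figure is printed in Table 1, to which the paragraph points. The low end of the range, where text and table agree at 84.3%, is the case that tests the adequacy of the design. At 13.5%, 93.3% is still ample. Sample size, margin, alpha and analysis do not depend on the wrong number. All of that stands, and it bounds the consequence: the error misstates the design's performance but does not undermine the design.

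It can also be said that the true relative risk is not stated, and that power near 99.9% does appear if low-dose is truly better: at a true relative risk of 0.90 the log-scale calculation gives 99.9%, and at 0.95 it gives 98.7%. This does not rescue the text. The protocol nowhere states such an assumption, and it does not fit the other Table 1 entries, which a true relative risk of 1 reproduces.

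Finally, the figure of about 90% concerns the scale of the calculation and is separate from the contradiction between text and table. That is fair. The contradiction stands without it.

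**Conclusion.** The text figure is wrong. At 13.5% incidence the stated inputs give 93.3%, as in Table 1, and about 90% on the relative-risk scale of the planned analysis. The type II risk is 100 − 93.3 = 6.7%, about 1 in 15 (10.2%, about 1 in 10, on the relative-risk scale), where the text implies less than 0.1%. By the protocol's own table the risk is understated more than 60-fold.

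This rests on 4,950 evaluable per arm, treated as independent observations, and on a true relative risk of 1. The preeclampsia sentence just before also ends on a figure above 99.9%, so a carry-over is likely, but the document cannot show it.

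**What to change.** In the Sample size text, replace the power stated for preterm birth at 13.5% with 93.3%, so that it matches Table 1. If the sponsor prefers to state power on the scale of the planned analysis, the figure is about 90%; the whole of Table 1 and the matching sentences should then be recalculated, because changing this cell alone would create a new mismatch.

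The cost is one corrected number, or one recalculated table under the second option. The stated power becomes less favourable. Sample size, margin, analysis and conduct stay as they are.
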